## Abstract

**Background and objectives:**

Recent molecular landscape studies characterizing lung cancer mostly utilize single tumor regions, ignoring tumor heterogeneity and evolutionary patterns. To address this issue, the TRAcking NSCLC Evolution through therapy (TRACERx) Consortium established a multiregion sampling of Western lung cancer to investigate its longitudinal evolutionary dynamics. Due to ancestral differences, there are still major gaps in understanding oriental lung cancer.

**Methods:**

We have established a prospective cohort of patients with non-small cell lung cancer (NSCLC) named Chinese lung cancer evolution and microenvironment tracking under therapy (CLEVER) study.

**Discussion:**

By acquiring comprehensive genetic variation data and clonal events from multiple regions of the tumor, we aim to decipher the molecular evolution code of Chinese lung cancer. The analysis of cell composition and spatial structure further characterizes the remodeling effects of tumor evolution and neoadjuvant therapy on the tumor microenvironment, helping to identify important markers that influence treatment effectiveness and recurrence. By monitoring mutations using a personalized minimal residual disease (MRD) panel from tumors at baseline, we can trace evolutionary significance and clonality, aiding in therapy decisionmaking. The CLEVER study significantly contributes to the development of personalized treatment strategies for lung cancer patients, enhancing outcomes and tailoring interventions to individual patient profiles.

## Introduction

Lung cancer, with non-small cell lung cancer (NSCLC) accounting for 85% of cases, stands as the malignancy with the highest mortality worldwide.^[1]^ An increasing body of cancer research has led to an unprecedented view of the molecular landscape of lung cancer throug next generation sequencing techniques, including DNA sequencing and RNA sequencing.^[2,3]^ Tumor evolution, as a key concept in understanding the onset and progression of cancer, not only contributes to tumor heterogeneity but also results in individual treatment differences. Through multi-region sampling and advanced sequencing technologies, researchers can uncover the evolutionary trajectories of tumors across different temporal and spatial scales. As the largest study of the evolution of NSCLC to date, the TRAcking NSCLC Evolution through therapy [Rx] (TRACERx) study employs multi-region sampling to investigate various aspects of lung cancer, including clonal evolution, genomic instability, and intratumoral heterogeneity to identify prognostic biomarkers that can inform treatment strategies and improve patient outcomes.^[4, 5]^ However, this study primarily involves patients of Western ancestry, which means it provides valuable insights into the biological mechanisms and progression of lung cancer within this specific population.

Lung cancer has significant racial differences, with significant variations in incidence, progression, and outcomes across different ethnic groups.^[6]^ These disparities are influenced by a complex interplay of genetic, environmental, and lifestyle factors. Studies have shown that genetic mutations, such as those in the EGFR and ALK genes, occur at different frequencies in Eastern and Western populations, leading to variations in treatment responses and prognoses.^[7, 8]^ Furthermore, a study comparing 305 cases of lung adenocarcinoma in individuals of East Asian ancestry with 249 cases in individuals of European ancestry found that the East Asian group exhibited more stable genome, characterized by fewer mutations and copy number changes. This finding highlighted important ancestry differences in lung cancer between Eastern and Western populations.^[9]^ However, for the eastern lung cancer multi-region lung cancer study, the explorations were limited due to the small sample size.^[10, 11]^ To sum up, it is necessary and urgent to establish a large multi-region sampling cohort of Chinese lung cancer population.

In our preliminary retrospective investigation of 81 patients with stage I NSCLC (Chinese PKUPH cohort, named CHN-P), we observed that there are strong ancestry disparities in lung cancer and Asian NSCLCs exhibit diverse genomic features. Regrettably, only a small number of patients, all of whom were at stage I, and the multi-region sampling methods were not consistent.^[12]^ To deepen our understanding of intratumoral heterogeneity in Chinese lung cancer patients, we expanded our study to include patients with stage I-IIIA NSCLC and implemented a standardized multi-region sampling process. This approach not only allowed us to explore the molecular signatures and clonal evolution inside tumors but also enabled us to investigate the immune microenvironment in the marginal zone and normal lung tissue. By uncovering the evolutionary molecular mechanisms and changes in the immune microenvironment from normal to aggressive borderline to tumor, we aim to provide valuable insights for clinical diagnosis and treatment strategies of lung cancer. With the prevalence of neoadjuvant therapy and its limited clinical benefits, there is a growing interest in identifying biomarkers and immune characteristics that are related to therapeutic efficacy. Hu *et al*. mapped tumor microenvironment changes during neoadjuvant immunotherapy by utilizing single-cell sequencing on tumor and peripheral blood samples and identified FCRL4+FCRL5^+^ B cells, CD 16^+^CX3CR1^+^ monocytes, and plasma estrogen changes as novel biomarkers.^[13]^ Xia *et al*. found a positive correlation between TYROBP expression and favorable responses to neoadjuvant camrelizumab, which was associated with increased infiltration of CD8^+^ T cells and enhanced effector responses of natural killercells.^[14]^ However, there have been no studies employing multi-region sampling cohorts for multi-omics research to explore the association of tumor heterogeneity with neoadjuvant efficacy and long-term survival. This study addresses this gap by innovatively collecting multi-region samples post-neoadjuvant therapy to investigate spatial regression patterns of tumors and changes in intratumoral heterogeneity. Furthermore, we have integrated various advanced spatial omics technologies to gain a more comprehensive understanding of the molecular landscape under neoadjuvant therapy.

The Chinese lung cancer evolution and microenvironment tracking under therapy (CLEVER) cohort study is a prospective single-center lung cancer multi-region sample cohort. This study examines how tumor evolution and intratumoral heterogeneity influence cancer treatment, outcomes, and prognosis. This protocol outlines the procedures for the CLEVER study (Version 1) and was prepared in accordance with the SPIRIT reporting guidelines.^[15]^

## Study design and highlights

We conduct a prospective large-scale multi-region Chinese lung cancer cohort called CLEVER study from Peking University People’s Hospital. The cohort is divided into two subcohorts: the naïve cohort, which includes patients who have not received neoadjuvant therapy before surgery, and the neoadjuvant cohort, which includes those who have. During surgery, samples of tumor tissue, marginal tissue, and matched normal tissue are collected. These samples undergo comprehensive multidimensional omics analyses, including whole exome sequencing (WES), RNA sequencing (RNA-seq), single-cell sequencing, and multiple spatial omics techniques such as Stereo-seq, digital spatial profiling (DSP), and imaging mass cytometry (IMC). Additionally, preoperative blood samples are collected on the morning of the surgery, and postoperative blood samples are collected during a two-year follow-up period for longitudinal dynamic monitoring of minimal residual disease (MRD) (Figure 1A). The primary endpoint of the study are two-year disease-free survival (DFS) and overall survival (OS). The secondary endpoint is to identify available predictors of clinical benefit.

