##### Consideration for survival analysis

In the first phase of the CLEVER study, we aim to compare 2-year DFS between predefined high-risk and low-risk groups using a two-sided log-rank test at α = 0.05 and 80% power (1-β = 0.80). Based on our preliminary data (CHN-P cohort),^[12]^ we assume a 2-year DFS event (recurrence or death) rate of 25% in the overall population. We further posit that the high-risk group will experience a hazard ratio (HR) of 2.0 relative to the low-risk group.

Applying the Freedman formula for survival comparisons:^[16]^

$$N_{\text{events }}=\frac{{\left(Z_{1-\frac{\alpha }{2}}+Z_{1-\beta }\right)}^{2}}{(\ln HR{)}^{2}}=\frac{(1.96+0.84{)}^{2}}{(\ln2{)}^{2}}\approx 43\text{ events }$$

Assuming a 25% event rate, at least 172 patients are needed to observe the required number of DFS events.

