##### Consideration for machine learning modeling

The novel lung cancer recurrence prediction model will be constructed based on machine-learning algorithms (section 5.2). For the model development, we adopt a ratio of 6:2:2 for the training, validation, and test sets. This division ratio is based on the consideration that 60% training provides adequate data for model fitting and feature selection, while 20% validation allows unbiased hyperparameter tuning, and 20% test ensures a fully held-out assessment to guard against overfitting. This ratio balances model complexity and evaluation rigor, as recommended for medium-sized cohorts.^[21, 22, 23]^ When 173 patients are recruited for statistical power in the training set, a total of 289 cases are required.

In summary, to address the above three dimensions of statistical consideration and the disruption caused by loss to follow-up, we plan to enroll 300 patients in the first phase. This provides sufficient power for survival analysis while also accommodating downstream modeling requirements.

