### Statistical analysis

The Wilcoxon test is used to compare distribution differences in genomic and transcriptomic biomarkers between groups, while Fisher’s exact test is applied to compare clinical variables and the number of gene mutations between groups. All p-values are two-sided, with *P* < 0.05 considered statistically significant.

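### Overall survival is a joint primary endpoint with two-year DFS, but the first-phase sample size gives it no power basis and the two endpoints have no stated decision rule

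*Protocol article*

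**What the plan says.** The section on study design and highlights states: "The primary endpoint of the study are two-year disease-free survival (DFS) and overall survival (OS". Both endpoints have the same rank, and nothing is said about how they combine.

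Under the sample size heading, the consideration for survival analysis concerns DFS only. The aim is to "compare 2-year DFS between predefined high-risk and low-risk groups", "using a two-sided log-rank test at α = 0.05 and 80% power (1-β = 0.80"). The inputs are "we assume a 2-year DFS event (recurrence or death) rate of 25% in the overall population" and that "the high-risk group will experience a hazard ratio (HR) of 2.0 relative to the low-risk group". The result is 43 events, and "at least 172 patients are needed to observe the required number of DFS events".

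After two further considerations on the prediction model, the plan settles on 300 patients for the first phase and concludes: "This provides sufficient power for survival analysis while also accommodating downstream modeling requirements". That sentence does not restrict survival analysis to DFS.

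Three other places matter:

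- The statistical analysis section says "All p-values are two-sided" and sets P < 0.05 as the general threshold.
- The patient management section fixes follow-up at two years.
- The section on confounding bias correction says OS will be modelled alongside DFS.

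**The concern.** A primary endpoint should have some basis for the belief that the study can answer it. For OS there is none. The shortfall in events is also structural: under the plan's DFS definition, patients who die within two years are a subset of those with a DFS event. Patients alive after recurrence when follow-up ends at two years contribute to DFS but not to OS.

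Two things are at stake. First, a non-significant OS comparison in the first phase could be read as evidence on a primary endpoint when it may reflect too few deaths. Second, with two primary endpoints and no statement of whether one or both must succeed, the type I error of the primary conclusion is not determined by the article.

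**Working it through.** **Inputs from the protocol article**

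- First-phase N = 300; two-year DFS event rate 25%; hazard ratio 2.0; two-sided alpha 0.05; power 80%.
- A DFS event is recurrence or death.
- Maximum acceptable loss to follow-up is 10%.
- Total recruitment target is over 1000.

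**Assumptions, because the article gives no figure**

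- Equal risk groups (a 30:70 split is shown as a check).
- The DFS hazard ratio of 2.0 applied to OS.
- The two-year death rate, shown as a range.

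**1. The plan's own figure.** The printed formula gives (1.96 + 0.84)² / (ln 2)² = 7.84 / 0.4805 = 16.3, not 43. The Schoenfeld formula with equal groups gives 4 × 16.34 = 65.3, so 66 events; Freedman's gives 71. Only the last step, 43 / 0.25 = 172, reproduces. That error is a separate matter. Here it means that 66, not 43, is the benchmark for 80% power.

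**2. Ceiling on OS events.** Deaths ≤ DFS events = 0.25 × 300 = 75.

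**3. Power for OS.** Power = Φ(√(d/4) × ln 2 − 1.96), where d is the number of deaths among 300 patients. For example, d = 30 gives √7.5 × 0.693 − 1.96 = −0.06, so 48%.

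| Two-year mortality (assumed) | Deaths | Power |
|---|---|---|
| 5% | 15 | 27% |
| 10% | 30 | 48% |
| 15% | 45 | 64% |
| 20% | 60 | 77% |
| 22% | 66 | 80% |
| 25% (every DFS-event patient dead) | 75 | 85% |

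Reaching 80% needs 66 / 300 = 22% mortality, which is 66 / 75 = 88% of the patients with a DFS event.

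**4. Sensitivity.**

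- With 10% loss (N = 270), power is 25%, 44%, 60% and 72% at 5%, 10%, 15% and 20% mortality. The 66 deaths then need 66 / 270 = 24.4% mortality.
- With a 30:70 split, even 75 deaths among 300 give only 78.5%.
- The prediction-model section expects 80 events rather than 75. Taking those as the ceiling, the required fraction is still 66 / 80 = 82.5%.

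**5. DFS for comparison.** With 75 events and equal groups, DFS has 85% power (81% with 10% loss). The closing power statement is therefore supportable for DFS under these assumptions.

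**6. Type I error, if either endpoint at 0.05 counts as success.** From a bivariate normal, the probability that at least one |Z| exceeds 1.96 under the null is:

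- 9.1% at correlation 0.5
- 8.3% at correlation 0.7
- 7.8% at correlation 0.8
- 7.0% at correlation 0.9

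Independence would give 1 − 0.95² = 9.75%, but shared events imply positive correlation, so that figure is not the relevant one. If both endpoints must be significant, the rate is at most 5%.

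**The case against.** The strongest defence is that the article never claims power for OS. The explicit 80% belongs to the DFS comparison, and the closing sentence sums up a consideration that was itself DFS-only. This stands. It would be wrong to set the OS power figures against a stated 80%, as though the plan had promised that for OS. What remains is that the closing sentence is unrestricted in a study where OS is also primary, so a reader can take it to cover OS.

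Second, the endpoints are those of the whole study, which aims for over 1000 patients, while the 300 are the first phase. This also stands. If 20% to 50% of DFS-event patients had died (an assumption), 1000 patients would give 0.25 × 1000 × 0.2 = 50 to 0.25 × 1000 × 0.5 = 125 deaths. The same formula then gives about 69% to 97% power, and 66 deaths would be only 6.6% mortality. The shortfall is thus specific to a first-phase OS comparison. The article describes no powered OS analysis at a later phase.

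Third, a reader might infer that the primary error rate exceeds 5%. The document does not support that as a fact. It states no success rule, specifies a time-to-event test at 0.05 for DFS only, and gives P < 0.05 as a general threshold. A multiplicity rule may also sit in an analysis plan that is not shown, so its absence from the article is not itself the finding.

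An analysis plan could settle the decision rule. It could not raise the ceiling on deaths, which follows from the endpoint definition, sample size, event rate and follow-up stated here.

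**Conclusion.** The point holds in limited form. OS is named primary alongside DFS, yet the sample size rationale rests on DFS alone. In the first phase, OS would reach 80% power at a hazard ratio of 2.0 only if about 88% of the patients with a DFS event had died by two years. This rests on equal groups, the plan's 25% DFS rate and the DFS hazard ratio carried over to OS. Actual OS power cannot be stated, because the article gives no death rate.

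The error-rate issue is conditional: about 7% to 9% for correlations of 0.9 to 0.5 if either endpoint suffices, and at most 5% if both are needed. Under the latter rule, however, the chance of overall success cannot exceed the power for OS. This should be corrected; it does not undermine the DFS comparison, which has about 85% power at 75 events.

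**What to change.** - In the section on study design and highlights, name two-year DFS as the single primary endpoint of the first phase and OS as secondary, reported with estimates and confidence intervals. A powered OS comparison could be left to the full cohort, with its own event rate and effect size stated.
- In the closing paragraph of the sample size section, limit the power statement to DFS.

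With a single first-phase primary endpoint, the either-or-both question no longer arises for that phase.

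No extra patients or procedures are needed. The cost is that OS loses primary status in the first phase. Because recruitment began in April 2022, the change to the protocol and the registry record must be made as a documented amendment to an ongoing study.

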**Figure 1 j_jtim-2025-0047_fig_001:**
[figure not shown]
Overview of CLEVER study. (A) Study design and scheme. (B) Key questions and highlights of this study. Image created by BioRender. com, with permission. CLEVER: Chinese Lung cancer EVolution and microEnvironment tracking under theRapy; FFPE: formalin fixation and paraffin embedding; WES: whole-exome sequencing; RNA-seq: RNA sequencing; ScRNA-seq: single cell RNA sequencing.

The CLEVER study aims to comprehensively characterize tumor evolution and immune microenvironment profiles of Chinese NSCLC, establishing accurate prognostic machine learning model and dynamic longitudinal MRD recurrence monitoring system. It investigates the entire process of tumor initiation, development, and treatment, addressing several key unresolved questions: (1) mutation accumulation and clonal evolution of normal lung tissue; (2) invasive molecular behaviors and microenvironment characteristics at the tumor-normal tissue interface; (3) unique evolutionary events and molecular profiles of Eastern lung cancer compared to Western lung cancer; (4) mechanism of tumor heterogeneity and ethnic differences; (5) the heterogeneous molecular landscape of lung cancer under neoadjuvant therapy; and (6) clinically available biomarkers of recurrence and metastasis. Through multi-site sampling and multi-omics analysis, this study aims to provide a deeper and clearer understanding of these questions, which constitutes a significant highlight of the research (Figure 1B).

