### Whole exome sequencing and analysis

The DNA library is prepared with an input of 200 ng genomic DNA using the VAHTS Universal Plus DNA Library Prep Kit for Illumina V2. The subsequent hybridization capture is performed using the SureSelect XT target enrichment system. The final DNA library is quantified using the Qubit 3.0 and fragment detection is conducted with the Agilent 2100. Finally, the DNA library is sequenced using paired-end 150 bp reads on the Illumina NovaSeq 6000 platform.

The sequencing data is analyzed using the WES pipeline. The sequencing data from white cells is used to exclude germline mutations. Clean reads in FASTQ format are aligned to the human UCSC reference genome (hg19/GRCh37) using the Burrows-Wheeler Aligner (BWA, v0.7.15). Sambamba (v0.6.8) is used to process PCR duplicates in the mapped BAM files. The Genome Analysis Toolkit (GATK v4.0.11.0) is employed for local realignment and base quality recalibration to compute sequencing coverage and depth. Single nucleotide variations (SNVs) and small insertions and deletions (Indels: < 50 bp) are identified using GATK MuTect2 (v1.1.4). Multiple testing correction for gene-level mutation frequency comparisons will be performed using the Benjamini-Hochberg procedure, with an adjusted p-value (FDR) cutoff of < 0.05.

Based on multi-region sequencing, region-based tumor mutation calling is combined to recall tumor-informed mutations, allowing for the acquisition of new recalled mutations for each region. Using these recalled region-level mutations, the phylogenetic tree is reconstructed using the CNIPHER method,^[24]^ enabling the identification of clonal and subclonal mutations. Somatic copy number alterations (SCNAs) are processed using ASCAT (V2.3), which allows for the determination of intratumoral heterogeneity in both SNVs and SCNAs, specifically assessing subclonal mutation fractions and subclonal SCNAs fractions. This comprehensive analysis facilitates a deep understanding of evolutionary events within the tumor, characterized by intratumoral heterogeneity, clonal illusion, subclonal expansion, whole genome doubling, weighted genome integrity index (wGII), and loss of heterozygosity (LOH). These insights provide a detailed depiction of the tumor’s evolutionary landscape and its underlying genetic dynamics.

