#### Confounding bias correction

To control for baseline imbalances between the neoadjuvant and naïve cohorts, we will implement the three methods as follows: (1) Propensity Score Matching (PSM): A logistic regression–derived propensity score will be used for 1: 1 nearest-neighbor matching (caliper = 0.2), including age, sex, smoking status, clinical stage, and ECOG performance status. Balance will be checked *via* standardized mean differences (<0.1). (2) Multivariable Regression: DFS and OS will be modeled in the unmatched full cohort, adjusting for the same covariates to verify robustness. (3) Subgroup Analyses: Pre-specified stratified analyses by clinical stage (I *vs*. II–IIIA) and ECOG (0 *vs*. 1) will be performed. Interaction p values will assess heterogeneity of treatment effect.

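### Eastern-versus-Western differences are a key question, but the stated between-group tests are unadjusted and confounding control covers only neoadjuvant versus naïve, so case mix could be read as ancestry

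*Protocol article*

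**What the plan says.** Under Study design and highlights, the numbered key questions include "unique evolutionary events and molecular profiles of Eastern lung cancer compared to Western lung cancer; (4) mechanism of tumor heterogeneity and ethnic differences". The Introduction justifies the cohort largely by ancestry. It also says of racial differences in lung cancer: "These disparities are influenced by a complex interplay of genetic, environmental, and lifestyle factors".

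The methods that could bear on this comparison are:

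- **Statistical analysis.** "The Wilcoxon test is used to compare distribution differences in genomic and transcriptomic biomarkers between groups", and for categorical data Fisher's "exact test is applied to compare clinical variables and the number of gene mutations between groups". The threshold is: "All p-values are two-sided, with *P* < 0.05 considered statistically significant". No covariates or strata are named, and the groups are not identified.
- **Whole exome sequencing and analysis.** "Multiple testing correction for gene-level mutation frequency comparisons will be performed using the Benjamini-Hochberg procedure", at an FDR below 0.05.
- **RNA sequencing and analysis; GeoMx digital spatial profiling.** DESeq2 and DESeq-based analyses with Benjamini-Hochberg correction, and no stated design covariates.
- **Confounding bias correction.** The purpose is set out as "To control for baseline imbalances between the neoadjuvant and naïve cohorts". Propensity matching uses age, sex, smoking, clinical stage and ECOG status. The regression adjustment models DFS and OS, not molecular features.

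The article does not name the Western dataset for the comparison or describe its composition.

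**The concern.** Eastern and Western tumours would come from separately assembled cohorts. An unadjusted Fisher or Wilcoxon test asks whether the two cohorts have the same marginal frequency or distribution. If the cohorts differ in a factor that affects the feature, that hypothesis is false even when ancestry has no effect within levels of the factor. Smoking is the obvious example; stage, histology and prior treatment work the same way.

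Benjamini-Hochberg correction limits the share of false rejections of the hypothesis actually tested. Here that hypothesis is marginal equality, so a gene that differs only through case mix counts as a correct discovery and passes the correction.

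The authors recognise non-genetic causes in the Introduction, and they adjust for smoking, sex and stage in another contrast. The contrast that motivates the cohort has no such provision. At stake is whether a reported Eastern-Western difference can be attributed to ancestry at all.

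**Working it through.** The article gives no sample size, power or error rate for this comparison, so there is no figure of its own to reproduce. The check is whether the mechanism works at the study's scale, and how far the answer depends on assumptions.

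**Inputs from the article**
- 300 Chinese patients (first phase) and a long-term aim of over 1000 (Sample size calculation).
- Two-sided 0.05 (Statistical analysis).

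**Assumed inputs**
- 421 Western patients. The Discussion gives this as the size of a Western multi-region cohort but does not name it as the comparator.
- The share of smokers in each cohort, and the mutation frequency in never-smokers and smokers. None of these is in the article, so ranges are shown.
- No ancestry effect: mutation depends on smoking only.

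**One case by hand.** Smokers 50% East and 70% West; gene mutated in 40% of never-smokers and 20% of smokers.
- East: 0.50 × 0.20 + 0.50 × 0.40 = 0.30.
- West: 0.70 × 0.20 + 0.30 × 0.40 = 0.26.
- Standard error: √(0.30 × 0.70/300 + 0.26 × 0.74/421) = 0.0340.
- Standardised difference: 0.04/0.0340 = 1.18.
- Approximate rejection probability: Φ(1.18 − 1.96) = Φ(−0.78) ≈ 0.22.

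Simulation of Fisher's test gives 22.2% for this case.

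**Simulated rejection rates, 300 v 421, 2000 replicates per row**

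| Smokers East / West | Mutated: never-smokers / smokers | Fisher, unadjusted | Mantel-Haenszel by smoking |
|---|---|---|---|
| 50% / 50% | 50% / 10% | 3.8% | 4.4% |
| 50% / 90% | 20% / 20% | 5.2% | 5.5% |
| 60% / 70% | 30% / 20% | 5.8% | 4.8% |
| 60% / 70% | 50% / 10% | 23% | 4.7% |
| 50% / 70% | 40% / 20% | 22% | 5.2% |
| 50% / 70% | 50% / 10% | 66% | 5.6% |
| 50% / 90% | 40% / 20% | 66% | 4.9% |
| 50% / 90% | 50% / 10% | 100% | 5.6% |

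The first two rows are controls. With an equal smoking mix, or with no effect of smoking, Fisher's test behaves as it should. Inflation needs both an imbalance and a link.

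**Wilcoxon on a continuous feature**, with smoking shifting the mean by an assumed number of standard deviations:
- 60%/70% smokers and 0.3 SD: 7%.
- 50%/70% and 0.5 SD: 23%.
- 50%/90% and 0.5 SD: 72%.
- No shift, or equal mix: about 5%.

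**Effect of enrolling more patients.** Repeating the hand-worked case with 1000 Chinese patients, the standard error falls to √(0.21/1000 + 0.1924/421) = 0.0258. The standardised difference rises to 1.55, and Φ(1.55 − 1.96) ≈ 0.34. Simulation gives 33% for Fisher and 5.4% for Mantel-Haenszel. A larger cohort makes confounding easier to detect as a difference; it does not remove it.

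**The case against.** The strongest reply is that nothing in the article assigns Fisher or Wilcoxon to East versus West. The section speaks only of groups, and a condensed article may leave covariates and comparator handling to a fuller document. This stands in part: applying these tests here is an inference by default. But the article does not leave confounding wholly to another document. It gives matching covariates, a caliper, a balance threshold and subgroups, and directs all of them at one contrast.

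A second reply is that the key question may be descriptive. For a plain population contrast, a marginal difference is not a false positive, whatever its cause. That is right, and it is why labelling is part of the fix. The question on ethnic differences and their mechanism, and the ancestry rationale in the Introduction, invite the causal reading.

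A third is that the primary endpoints are DFS and OS, and the cohort is not sized for this comparison. That limits the weight of the point but does not remove it.

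Stronger readings that a reader might infer, and that the document does not support:
- *Case-mix differences will be reported as ancestry effects.* No Western comparator or case mix is given, so one can say only that they could be.
- *Error rates are far above 5% for every smoking-linked gene.* With a weak link or similar mix, the rate stays near 5%.
- *Fisher and Wilcoxon are the only tests.* DESeq2 and DESeq-based analyses are also named.
- *Post-neoadjuvant tumours will be pooled against Western cases.* The article defines two subcohorts and gives neoadjuvant disease its own key question. It neither states nor excludes pooling here.

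**Conclusion.** The point holds in conditional form. The tests stated for between-group molecular comparisons are unadjusted, and the stated confounding control does not reach the Eastern-Western contrast. Followed as written, the plan could not separate ancestry from smoking, stage, histology or prior treatment.

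The size cannot be fixed from the document. In the scenarios run, with no ancestry effect, Fisher's rejection rate goes from about 5% to nearly 100%, while stratifying by smoking holds it between 4.4% and 5.6% at the first-phase size. These figures rest on the assumed comparator of 421, the assumed smoking shares and the assumed gene-smoking links. They show the mechanism and its range and do not predict CLEVER's results. Only smoking was simulated; the argument for stage, histology and prior treatment is by analogy.

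The change is worth making because the question is central to the study's rationale and the remedy is cheap.

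**What to change.** Add a short paragraph to the statistical analysis section that does the following:

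1. Names the Western dataset and the covariates it holds.
2. Bases the Eastern-Western molecular comparison on the naïve cohort.
3. Stratifies or adjusts for smoking, histology, sex and stage: Mantel-Haenszel or logistic regression for gene-level mutation, regression or stratified Wilcoxon for heterogeneity measures, and the same covariates in the DESeq2 design.
4. Applies Benjamini-Hochberg to the adjusted P values.
5. Describes any unadjusted result as a cohort difference, not an ancestry difference.

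The cost is wording and modest extra analysis. CLEVER already records sex, smoking and histopathology (Patient management) and uses clinical stage in its propensity score, so recruitment and sampling do not change. The price is precision: neoadjuvant patients leave this comparison, as do Western cases lacking a covariate.
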